### Safety reporting

The risks for the two groups are those particular to TKR and from an operative intervention. This includes infection, thrombosis, stiffness, instability, pain, scar sensitivity, loss of function, nerve or vessel injury, requirement for revision with attendant time off work. General risks include cardiorespiratory risk, angina, MI, stroke, pneumonia, risks from prolonged recumbency, urinary infection, skin ulcers. Potential risks and steps taken to minimise these risks are outline in the PIL. In addition it is anticipated that those patients with patients who are randomised to use of the robotic instrumentation may require a longer procedure of up to 5 min [10], and there is a theoretical increased risk of infection. There is also a small (1%) risk of sustaining a fracture through a tracker pin (a threaded pin inserted into the bone so the robot can establish the position of the bone in time and place) [30, 31]. Tracker pins are routinely used for navigated TKR surgery and this increased risk is accepted to enable more accurate placement on the knee prosthesis. However, to our knowledge, there is no reported case of a fracture through a tracker pin site when used for robotic TKR surgery. There is also a small risk (1%) of wound infection at the site of tracker pins, but again these are established and accepted in navigation TKR surgery [32].

An adverse event (AE) is any untoward medical occurrence in a patient or other clinical investigation participant taking part in a trial of a medical device, which does not necessarily have to have a causal relationship with the device under investigation. An AE can therefore be any unfavourable and unintended sign (including an abnormal laboratory finding), symptom or disease temporally associated with the use of the device, whether or not considered related to the device.

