An adverse device effect (ADE) is all untoward and unintended responses to the medical device. The phrase ‘responses to a medical device’ means that a causal relationship between the device under investigation and an AE is at least a reasonable possibility, i.e. the relationship cannot be ruled out. All cases judged by either the reporting medically qualified professional or the sponsor as having a reasonable suspected causal relationship to the device qualifies as a device effect. This also includes any event resulting from insufficiencies or inadequacies in the instruction for use or deployment of the device and includes any event that is a result of a user error.

A device deficiency (DD) is inadequacy of a medical device related to its identity, quality, durability, reliability, safety, or performance, such as malfunction, misuse or use error and inadequate labelling.

‘Serious’ in serious adverse event (SAE) means an adverse event resulting the following: death, in-patient hospitalisation or prolonged hospitalisation (defined as an inpatient admission, regardless of length of stay). However, hospitalisation for pre-existing conditions (including elective procedures that have not worsened) or additional elective hospitalisation does not constitute a SAE. A life-threatening illness or injury in the definition of ‘serious’ refers to an event in which the participant was at risk of death at the time of the event; it does not refer to an event which hypothetically might have caused death if it were more severe. Persistent or significant disability or incapacity. Congenital anomaly or birth defect. Other serious events that may jeopardise the patient and may require medical or surgical intervention to prevent one of the other five listed outcomes. This includes device deficiencies that might have led to an SAE if suitable action had not been taken, intervention had not been made or if circumstances had been less fortunate.

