To ensure no confusion or misunderstanding of the difference between the terms ‘serious’ and ‘severe’, which are not synonymous, the following note of clarification is provided: The term ‘severe’ is often used to describe the intensity (severity) of a specific event (as in mild, moderate, or severe myocardial infarction); the event itself, however, may be of relatively minor medical significance (such as severe headache). This is not the same as ‘serious’, which is based on patient/event outcome or action criteria usually associated with events that pose a threat to a participant’s life or functioning. Seriousness (not severity) serves as a guide for defining regulatory reporting obligations.

A serious adverse device effect (SADE) is any untoward medical occurrence seen in a patient that can be directly related to the Stryker product resulting in resulting in any of the characteristics or led to characteristics of a serious adverse event. SADE is also any event that may have led to these consequences if suitable action had not been taken or intervention had not been made or if a circumstance has been less opportune. All cases judged by either the reporting medically qualified professional or the sponsor.

Anticipated serious adverse device effect (ASADE) which by its nature, incidence, severity or outcome has been previously identified in the current version of the risk analysis report or Investigator Brochure.

Unanticipated adverse device effect (UADE) is any serious adverse device effect on health or safety or any life-threatening problem or death caused by or associated with a device, if that effect, problem or death was not previously identified in nature, severity or degree of incidence in the investigational plan or application (including a supplementary plan or application), or any other unanticipated serious problem associated with a device that related to the rights, safety or welfare of the subject.

Tables 1 and 2 categorise the adverse event according to whether it is related to the device. Each AE will be assessed for seriousness, severity, causality and expectedness by an appropriately trained and delegated investigator. The Investigator, or an appropriately trained designee, should make an assessment of seriousness using the criteria in Table 3.

**Table 1 Tab1:** Classification of adverse event according to relation to the device (robot)

Adverse Events	Non-device related	Device or procedure related	
**Non-serious**	AE	ADE	

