**Serious**	SAE	SADE	
		Anticipated	Unanticipated
		ASADE	USADE

**Table 2 Tab2:** Device deficiency category according to SADE

Device deficiency	Could lead to a SADE	Would not lead to a SADE
**Category:**	Device deficiency with SADE potential	Device deficiency without SADE potential

**Table 3 Tab3:** Classification criteria for the intensity of the adverse event

Intensity	Description
Mild	An event easily tolerated by the patient, causing minimal discomfort and not interfering with everyday activities
Moderate	An event sufficiently discomforting to interfere with normal everyday activities
Severe	An event that prevents normal everyday activities

The expectedness of the AE will be assessed by the CI or an appropriately trained designee using the list of expected events below. This list is based on current clinical knowledge of expected intra- and post-operative complications of TKR. Intra-operative complications: not able to proceed with expected implant (in this case triathlon TKR), soft tissue damage, neurovascular damage, fracture, patients becomes medically unwell and cannot perform TKR, blood loss and general medical complications, e.g. heart attack, stroke. Post-operative complications: infection (superficial and deep implant infection), deep vein thrombosis and pulmonary embolus, stiffness, swelling, numbness, neurovascular complications, wound breakdown, fracture and general health problems, e.g. stroke, heart attack, kidney failure and potential loss of limb and life.

The relationship between the investigational medical device (including comparator treatments) and the occurrence of each AE must be assessed and categorised by the Chief Investigator (or delegate). Related events are those that are related to the administration of the medical device or study procedures. Each AE will be categorised as (1) not related (no relationship with the investigational device; other factor(s) certainly or probably causative) or (2) possibly related (the nature of the event, underlying medical condition, concomitant medication or temporal relationship make it possible that the AE has a causal relationship to the device).

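### Seriousness is to be judged from an intensity table, and the elective-admission exemption has no limit, so study-knee readmissions can be misclassified as non-serious

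*Protocol article*

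**What the plan says.** All of this stands in the Safety reporting section of the protocol article.

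- **Definition of serious.** The criteria are based on outcome and begin with "death, in-patient hospitalisation or prolonged hospitalisation (defined as an inpatient admission, regardless of length of stay". Life-threatening events, persistent or significant disability, congenital anomaly, and a residual criterion for events needing medical or surgical intervention to prevent a listed outcome are also covered.
- **Exemption.** Straight after the hospitalisation criterion, admission for pre-existing conditions is excluded. The sentence then adds that "additional elective hospitalisation does not constitute a SAE".
- **Serious versus severe.** A clarifying note says the two terms are not interchangeable and concludes: "Seriousness (not severity) serves as a guide for defining regulatory reporting obligations".
- **Instruction to investigators.** For each adverse event, the investigator or designee "should make an assessment of seriousness using the criteria in Table 3".
- **Table 3.** Its title is "Classification criteria for the intensity of the adverse event". It has three grades, and the highest is "An event that prevents normal everyday activities".
- **Named risks.** The risks of knee replacement listed at the start of the section include instability and "requirement for revision with attendant time off work".

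**The concern.** There are two separate faults in rules that investigators will apply.

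First, the criteria named for judging seriousness are not seriousness criteria. The section warns against confusing two concepts, and its instruction then sends the reader to the wrong one.

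Second, the exemption for elective admissions is not confined to admissions that have nothing to do with the trial. Repeat surgery on a replaced knee can be scheduled, so on a literal reading it falls inside the exemption. The Background says most early revisions are due to malalignment and instability, which are the two failures that the robot and the sensor are meant to reduce. The exemption therefore touches events that bear directly on the trial's question.

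At stake are the SAE classification and the reports that follow from it: one working day to the sponsor, 15 days to the ethics committee for related and unexpected SAEs, and the manufacturer's form for related SAEs. SADE status also borrows the characteristics of an SAE, so the device categories inherit the same ambiguity.

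**Working it through.** No arithmetic applies. The check sets the rules side by side and follows events through them.

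**1. Can Table 3 decide seriousness?** It has no entry for death, admission, threat to life or disability, and no cut-point between serious and non-serious. Table 1 uses the serious/non-serious split without defining it, and Table 2 sorts device deficiencies. The only usable criteria are in the running text, and the instruction does not point there.

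- *Event with moderate symptoms that leads to an unplanned admission.* Serious by the definition. Table 3 says moderate and is silent on seriousness.
- *Event that prevents everyday activities but meets none of the listed outcomes.* Not serious by the definition. Table 3 gives its highest grade.

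**2. Does a later step correct a wrong call?** The items listed for recording each event include severity but not seriousness. The chief investigator determines seriousness for events already raised as SAE, SADE, ASADE or UADE. No second check is stated for an event first judged non-serious.

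**3. How far does the exemption reach?** Pre-existing conditions have their own limb, so the limb on additional elective hospitalisation must cover something more. Nothing restricts it to admissions planned before enrolment, to another joint or to an unrelated illness.

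- *Planned revision of the study knee for instability.* It is an inpatient admission, so it meets the hospitalisation criterion. It is elective, so the exemption removes it. It may return through disability or through the residual intervention criterion, but each of these needs a judgement by the investigator. Neither revision nor instability is in the list of expected events. If the event were judged related and serious, the 15-day ethics report would therefore be in play as well as the sponsor report.
- *Planned readmission for stiffness.* It is exempt by the same route. Stiffness is on the expected list, so the 15-day report would not arise in any case. Only the sponsor report and the SAE count are exposed.

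**4. Is the event lost?** No. All adverse events go on the case report form whether or not they are attributed to the device (Safety reporting). Complications forms are completed at 3, 6 and 12 months (Recruitment), and complications are recorded at each visit (Outcome measures). Health service use is collected at 3, 6, 9 and 12 months (Recruitment; Outcome measures), and the economic data include inpatient stays (Statistical analysis). What is exposed is the label and the reporting clock.

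**The case against.** The strongest reply is that the Table 3 reference is a slip in cross-referencing, perhaps from condensing a longer protocol, and that the surrounding text repairs it. The outcome-based definition is given in full, the note on serious versus severe is emphatic, and Table 3 offers no rule that could be applied to seriousness. A careful investigator would go back to the definition. Much of this stands, and it keeps the point modest. It does not remove it, because the sentence is the instruction to the person making the call, and that person may be a designee.

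On the exemption, the reply is that only one route to seriousness is closed and that the authors probably meant admissions unconnected with the trial. The first part is right. The second is plausible, but the text does not say it.

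A reader might infer more than the document supports:

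- *That the comparison of harms between arms would miss re-operations.* The capture routes above do not depend on the SAE label and apply to both arms. A comparison of SAE rates is also not among the listed objectives.
- *That a severe symptom automatically becomes serious.* Table 3 maps no grade to serious, and the clarifying note rejects that equation.
- *That every safety step hangs on the seriousness call.* Device quarantine is also triggered by a device deficiency that could have led to a serious device effect, and the 15-day report covers only SAEs that are both related and unexpected.
- *That the loss can be put in percentage points of an arm's SAE rate.* The article gives no re-operation rate, so any such figure would rest on an invented count.

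**Conclusion.** Both faults are in the text and should be corrected. The seriousness instruction contradicts the section's own definition and its own note. The elective exemption, read as written, takes planned surgery on the study knee out of the hospitalisation criterion.

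The consequence is limited to possible misclassification: an event called non-serious, absent from SAE counts, and not reported to the sponsor within one working day, or to ethics within 15 days where it is related and unexpected. Its size cannot be stated. Follow-up is 12 months, while the Background counts revisions before 5 years as early and gives no figure for the first year. Clinicians know the allocation, so an unclear rule could be applied differently in the two arms. That is a possibility, not something the document shows.

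The conclusion assumes that investigators work from wording like that of the article. If the operational protocol carries a correct table reference and a narrower exemption, only the article needs correcting. The primary analysis and sample size do not depend on this.

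**What to change.** Make two changes in Safety reporting, with a short note to investigators:

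1. Point the seriousness assessment to the outcome-based criteria in the definition of a serious adverse event, and state that Table 3 is for severity only.
2. Limit the elective exemption to admissions planned before consent, or unrelated to the study knee, the index surgery or its complications. Naming the surgery and its complications matters, because a limit to the knee alone would still exempt a planned admission for a non-knee complication such as thrombosis. State that the rule applies identically in both arms.

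The cost is two sentences, the note, and a few more SAE forms. If the study is under way, adverse events already recorded with an elective admission should be re-read against the clarified rule.

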All AE’s occurring during the study observed by the investigator or reported by the participant, whether or not attributed to the device under investigation will be recorded on the CRF as specified in the protocol. All ADE’s will be recorded in the CRF. The following information will be recorded: description, date of onset and end date, severity, assessment of relatedness to device, other suspect drug or device and action taken. Follow-up information should be provided as necessary. The relationship of AEs to the device will be assessed by a medically qualified investigator or the sponsor/manufacturer and will be followed up until resolution or the event is considered stable.

All ADE that result in a participant’s withdrawal from the study or are present at the end of the study should be followed up until a satisfactory resolution occurs. All DDs should be reported to NUTH via the safety reporting inbox: [contact]

All SAEs/SADEs/ASADEs/UADEs will be reported to the CI in the first instance, who will determine seriousness, relatedness and expectedness. The event will then be reported to the sponsor/legal representative NUTH R&D Regulatory Compliance Team at [contact] within one working day of the investigator team becoming aware of them. For a related serious adverse event (SAE) the investigator will complete a Stryker ‘Product Experience Report’ form *(**www.stryker.com**product experience report)* or inform a Stryker employee*.*

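### The causality scale can file an event as not related when the adverse device effect definition counts it as a device effect, so a serious event can miss the reports that depend on relatedness

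*Protocol article*

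**What the plan says.** All the relevant text is in the Safety reporting section of the protocol article.

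**Thresholds.**
- The ADE definition is met when "a causal relationship between the device under investigation and an AE is at least a reasonable possibility, i.e. the relationship cannot be ruled out".
- The SADE definition covers "any untoward medical occurrence seen in a patient that can be directly related to the Stryker product" with a serious consequence.
- Table 1 puts ADE and SADE in the same device- or procedure-related column and separates them by seriousness alone. The later paragraph on quarantining devices likewise equates a serious ADE with a SADE.
- Each adverse event goes into one of two categories. The first is "not related (no relationship with the investigational device; other factor(s) certainly or probably causative". The second, possibly related, applies when the nature of the event, the underlying condition, concomitant medication or timing makes a causal link to the device possible.

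**Assessors.**
- The ADE definition takes in "All cases judged by either the reporting medically qualified professional or the sponsor as having a reasonable suspected causal relationship" to the device, so either judgement is enough. The SADE definition names the same two parties, in a sentence that is left incomplete.
- The two-category scale is completed by the Chief Investigator or a delegate.
- For serious events, the Chief Investigator is the one "who will determine seriousness, relatedness and expectedness".
- The paragraph on recording adverse events says that the relationship to the device is "assessed by a medically qualified investigator or the sponsor/manufacturer".

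**The concern.** The ADE definition sets a low bar: the device counts unless it is excluded. The first category of the scale sets a higher one, because the device can be set aside once another cause is judged probable. Patients having a knee replacement often have a plausible alternative cause for a complication, so events between the two bars are not a remote possibility. The SADE wording, taken alone, would raise the bar again for the more serious events.

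Relatedness is not just a label here. It decides whether the manufacturer is told, whether the device is quarantined as the source of a SADE and, together with unexpectedness, whether the ethics committee and the incident system are told. It also decides the cell of Table 1 in which the event is counted. Two assessors following the text in good faith could reach different answers on the same facts.

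**Working it through.** No arithmetic applies. The check takes one test case through each rule: a serious event for which another factor is probably causative but the device link is not excluded.

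**Step 1. Classification of the test case**

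| Text in Safety reporting | Result |
|---|---|
| ADE definition | Device effect, because the link is not excluded |
| SADE definition | Unclear; depends on whether the event can be *directly* related |
| Table 1 and quarantine paragraph | SADE, because it is a serious ADE |
| Scale, category 1 (not related) | Fits the *probably causative* limb, though not the opening words on there being no relationship |
| Scale, category 2 (possibly related) | Fits, because a causal link is possible |

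The two categories overlap for this case, and the text does not say which prevails.

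**Step 2. What follows from each filing**

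| Route | Trigger | If filed not related | If filed possibly related |
|---|---|---|---|
| Sponsor, one working day | Any serious adverse event | Made | Made |
| Manufacturer report | Related serious event | Not triggered | Triggered |
| Device quarantine | SADE, or a device deficiency that could have led to one | Not triggered through the SADE route | Triggered |
| Ethics committee, 15 days | Related and unexpected | Not triggered | Only if also unexpected |
| DATIX | Related and unexpected, or an unanticipated SADE | Not triggered | Only if also unexpected or unanticipated |

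**Step 3. The expectedness condition**

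The list of expected complications includes infection (superficial and deep), fracture and stiffness. For those events the ethics report and the general DATIX report are not due even if the event is classed as related. Instability is named among the risks of surgery but is not on the expected list, so for an event of that kind the relatedness category does decide those two reports.

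**Step 4. Assessors**

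Most of the descriptions fit together. A delegated investigator is covered by Chief Investigator or delegate, and serious events go to the Chief Investigator. Two points do not fit:
- Under the ADE definition a judgement by either the reporting professional or the sponsor is enough. Under the serious-event paragraph the Chief Investigator determines relatedness. If the sponsor sees a link and the Chief Investigator does not, the two rules give different answers.
- The recording paragraph sets the manufacturer beside the sponsor as a possible assessor. The ADE and SADE definitions do not name the manufacturer in that role.

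**The case against.** The strongest reply is that this is loose drafting with safeguards around it. Every serious event reaches the Chief Investigator and then the sponsor within one working day, whatever its relatedness, and the sponsor can then judge it a device effect under the ADE definition. Category 1 opens by requiring no relationship, and category 2 names the underlying condition among the things to weigh, so a careful assessor would choose possibly related. Table 1 and the quarantine paragraph show that a SADE was meant to be a serious ADE. The article is also condensed, and the full protocol or sponsor procedures may settle disagreements between assessors.

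Most of this stands, and it limits the consequence. Misfiling is permitted by the wording, not required by it. The absence of a rule for disagreements is not itself a finding. What the reply does not remove is that the printed category 1 includes a limb that the printed ADE definition excludes. The sponsor safeguard is also weakened by the sentence that gives the determination of relatedness to the Chief Investigator.

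A reader might infer more in four ways, none of which the document supports:
- **That such an event escapes expedited reporting altogether.** It does not; the sponsor report does not depend on relatedness.
- **That a deep infection wrongly filed would be kept from the ethics committee.** Deep infection is on the expected list, so neither that report nor the general DATIX report would be due in any case. Only the manufacturer report, the SADE route to quarantine and the SADE classification are at risk.
- **That one misfiled event could erase the safety signal.** The article gives about 1% each for tracker-pin fracture and pin-site infection, and 45 × 0.01 = 0.45 expected events in a 45-patient arm. But all adverse events are recorded whether or not they are attributed to the device, so a comparison of the arms does not depend on attribution. Pin-site events are also hard to attribute elsewhere, and events related to study procedures already count as related.
- **That the manufacturer may judge its own device alone.** The Chief Investigator or a delegate must still categorise every event.

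**Conclusion.** The conflict holds in a limited form. The ADE definition and category 1 of the scale apply different thresholds, the two categories overlap, and the word *directly* in the SADE definition does not match the article's own Table 1 and quarantine paragraph. A serious event whose device link is not excluded can therefore be filed as not related. It would then miss the manufacturer report and SADE-triggered quarantine and, if also unexpected, the 15-day ethics report and DATIX.

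The number of events affected cannot be estimated from the document. The point concerns safety classification and reporting, and it does not affect the primary outcome or its analysis. The conclusion assumes that assessors apply the two categories as printed and that no form or procedure outside the article overrides them. It is worth correcting because the remedy is small and uses the protocol's own rule.

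**What to change.** Apply the threshold of the ADE definition throughout the Safety reporting section:
- In category 1 of the scale, delete *or probably*, so that not related is used only when the device is excluded and every other event is possibly related.
- In the SADE definition, delete *directly*, so that a SADE is a serious ADE, as in Table 1.
- Reconcile the two assessor statements, the one naming the sponsor/manufacturer and the one under which the Chief Investigator determines relatedness, with the rule in the ADE and SADE definitions that a judgement by either the reporting professional or the sponsor is enough. Complete the unfinished sentence in the SADE definition at the same time.

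The cost is a few words in the protocol and a matching edit to the adverse event form. Slightly more events will be classed as related and reported.
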